**12.10 Appendix 10: ABC Research Process Feedback (Rating Scales + Open-ended Questions)**

**Research Process Feedback**

As you come to the end of the research study, we would appreciate your feedback on the whole research process.

This feedback is very valuable, as it will help us plan the larger study to best need women’s needs. Therefore, please be as honest as possible. Don't forget - your responses are anonymous!

Thinking back to the very beginning, was the **information provided about the** **study** clear? (i.e., were you able to understand what taking part would involve?)

|  | Not at all clear  1 | 2 | 3 | 4 | Very clear  5 |
| --- | --- | --- | --- | --- | --- |
| Please select one option: |  |  |  |  |  |

Was the **contact and** **communication** throughout the study appropriate? (e.g., were instructions clear? Did you feel comfortable?)

|  | Not at all appropriate  1 | 2 | 3 | 4 | Very appropriate  5 |
| --- | --- | --- | --- | --- | --- |
| Please select one option: |  |  |  |  |  |

Did you find the **questions in the** **questionnaires** **relevant?** (e.g., did the thoughts, feelings, and behaviors asked about reflect how body image concerns may have impacted you?)

|  | Not relevant at all  1 | Sometimes relevant  2 | Very relevant  3 |
| --- | --- | --- | --- |
| Please select one option: |  |  |  |

Did you find completing the **questionnaires tiring?**

|  | Not at all tiring  1 | 2 | 3 | 4 | Very tiring  5 |
| --- | --- | --- | --- | --- | --- |
| Please select one option: |  |  |  |  |  |

Would you like to explain or expand on any of the above answers?

___________________________________________________________________________________________________________________________________________________________________________________________________________________________________________________

Were you **already** **familiar** with the Macmillan ‘Body image and cancer’ booklet you were given before this study?

|  | Yes | No |
| --- | --- | --- |
| Please select one option: |  |  |

**How much** of this booklet did you read during this study?

|  | None of it | Less than a quarter of it | Up to half of it | Up to three quarters of it | The whole booklet |
| --- | --- | --- | --- | --- | --- |
| Please select one option: |  |  |  |  |  |

If you read **any** of the booklet, how **helpful** did you find it?

|  | Not at all helpful  1 | 2 | 3 | 4 | Very helpful  5 |
| --- | --- | --- | --- | --- | --- |
| Please select one option: |  |  |  |  |  |

If you did **not read** any of the booklet, could you please tell us why?

________________________________________________________________________________________________________________________________________________

Did you seek any **other support** for your body image during the study?

|  | Yes | No |
| --- | --- | --- |
| Please select one option: |  |  |

If you **did** seek other support, could you please tell us what this was?

________________________________________________________________________________________________________________________________________________

How helpful did you find this support?

|  | Not at all helpful  1 | 2 | 3 | 4 | Very helpful  5 |
| --- | --- | --- | --- | --- | --- |
| Please select one option: |  |  |  |  |  |

If you had been randomly allocated to the **other condition** (either the ABC programme or control group), do you think you would have continued with the study?

|  | Yes | Maybe | No |
| --- | --- | --- | --- |
| Please select one option: |  |  |  |

Could you please tell us why you selected this?

________________________________________________________________________________________________________________________________________________

How have you found the overall experience of **taking part in this study?**

|  | A very negative experience  1 | 2 | 3 | 4 | A very positive experience  5 |
| --- | --- | --- | --- | --- | --- |
| Please select one option: |  |  |  |  |  |

Do you have any other feedback on the whole study, or suggestions for improvement?

____________________________________________________________________________________________________________________________________________________________________________________________________________________________________________________________________________________________________________________________________

_________________________________________________________________________________

_________________________________________________________________________________

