We will collect a variety of different type of data exploring acceptability and feasibility. This will inform the design of a future definitive RCT and help refine intervention, recruitment, and retention procedures. Figure 1 provides an outline of participant flow in the study and Table 1 provides an outline of the different assessments and their associated timepoints.

- - 1. **Quantitative measures of feasibility and acceptability**

We will collect the following quantitative data to assess feasibility and acceptability of the research design and ABC:

- - - 1. **Monitoring data**
- Rates of recruitment (and associated response rates), with attention to the method by which women were recruited and their demographic diversity.
- Rates of retention following randomisation:
  - Proportion completing ABC (number of sessions attended and between-session activities completed)
  - Proportion of control arm reading the Macmillan body image booklet (plus percentage of booklet read)
  - Proportion completing outcome measures at each assessment (plus data completeness rates; outcome measures described in 5.6.3).
    - 1. **Self-report rating scales included in outcome assessments (see 5.6.3)**
- Rating scales to explore acceptability of ABC (e.g., the group format, online nature, between-session activities; Appendix 9) - to be completed by ABC participants in the immediate post-intervention assessment, i.e., Week 9.
- A single rating scale examining how helpful participants found the ABC programme will also be included in the three- and six-month follow up assessments (see Appendix 31). This will allow monitoring of how participants’ perceptions of the programme and its impacts may develop over time.
- Rating scales to explore acceptability of the research process generally (e.g., information provided about the study, randomisation process, questionnaires; Appendix 10) – to be completed by all participants in the six-month post-intervention assessment i.e., Week 32.
  - 1. **Qualitative measures of feasibility and acceptability**

In addition to the above, we will collect the following qualitative data to assess feasibility and acceptability of the research design and ABC:

- - - 1. **Open-ended questions included in outcome assessments (see 5.6.3)**

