Descriptive analyses (i.e., percentages and confidence intervals) will be conducted on numbers relating to recruitment (including numbers of eligible women who decide not to proceed after reading the PIS) and retention following randomisation, including numbers who complete ABC (i.e., number of sessions attended and between-session activities completed), who read the Macmillan body image booklet (in the control arm; including percentage of booklet read), and who complete self-report outcome measures at each assessment timepoint (including data completeness rates). We will assess the extent of missing data, withdrawals and loss-to-follow-up.

We will report data in line with the Consolidated Standards of Reporting Trials (CONSORT) 2010 Statement showing attrition rates and loss to follow-up.

- - - 1. **Self-report rating scales**

Descriptive analyses (i.e., means, standard deviations, percentages) will be conducted on the ratings scales related to acceptability of ABC (e.g., the group format, online nature, between-session activities; Appendix 9), as well as those related to acceptability of the research process generally (e.g., information provided about the study, randomisation process, questionnaires; Appendix 10).

- - 1. **Analysis of qualitative data**
       1. **Open-ended questions**

The responses to the open-ended questions asking for feedback on ABC (e.g., the group format, online nature, between-session activities; Appendix 9) and the research process generally (e.g., information provided about the study, randomisation process, questionnaires’ Appendix 10) will be analysed in NVivo using thematic analysis (Braun & Clarke 2006). The analytic process of ‘codebook’ thematic analysis will be used (Braun & Clarke 2006, 2022), whereby text will be coded using a priori codes and themes relating to feasibility and acceptability (informed by O’Cathain et al 2015).

- - - 1. **Interviews**

Interviews will be digitally recorded, transcribed verbatim, and analysed in NVivo using thematic analysis (Braun & Clarke 2006). The analytic process of ‘codebook’ thematic analysis will be used (Braun & Clarke 2006, 2022), whereby transcripts will be coded using a priori codes and themes relating to feasibility and acceptability (informed by O’Cathain et al 2015).

- 1. **Analysis of self-report outcome measures**

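### The booklet-reading item has no answer between three quarters and the whole, so the planned control-arm percentage read comes only as ranges, with an ambiguous top

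*Protocol*

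**What the plan says.** Protocol section 5.6.1.1 lists, among the retention measures after randomisation, "Proportion of control arm reading the Macmillan body image booklet (plus percentage of booklet read"). Section 7.1.1.1 repeats the measure for analysis: "in the control arm; including percentage of booklet read". The form of that analysis is given at the start of the same paragraph: "Descriptive analyses (i.e., percentages and confidence intervals) will be conducted on numbers relating to recruitment". Section 2 names control-arm reading of the booklet among the uncertainties to be settled before a definitive trial.

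The data come from Appendix 10, the research process feedback form, "to be completed by all participants in the six-month post-intervention assessment i.e., Week 32". The item asks how much "of this booklet did you read during this study" and requires one choice. After an option for none, the choices are "Less than a quarter of it | Up to half of it | Up to three quarters of it | The whole booklet". The two highest options, printed next to each other, are thus "Up to three quarters of it | The whole booklet".

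The interview schedules for women who completed the study (Appendices 15 and 16) also ask whether the whole booklet was read. They ask for no percentage, and section 5.6.2.2 plans interviews with only 16 to 20 participants.

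**The concern.** The options do not cover the whole range of possible answers. Someone who read more than three quarters but did not finish fits neither of the two highest options. The two "up to" options also have no printed lower bound.

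The response options are fixed in the questionnaire, so no later analysis rule can repair this. Once a 60-page reader has ticked the same box as a 77-page reader or a 50-page reader, the answers cannot be separated. The gap lies at the upper end of the scale, where engaged readers of the comparator would fall. Section 6.3 says that controls are encouraged to work through the booklet gradually, so near-complete readers are a group the study would want to recognise.

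**Working it through.** The protocol states no figure for booklet reading, so there is none to reproduce. The check maps each possible amount read to the printed options.

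**Inputs.** Booklet length 77 pages (section 6.3); options as printed in Appendix 10; control arm of 60 (Trial Summary).

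**Step 1: cut-points in pages.** 0.25 × 77 = 19.25; 0.50 × 77 = 38.5; 0.75 × 77 = 57.75. No whole page count falls on a boundary.

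**Step 2: read the options as ascending bands.**

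| Pages read | Page counts | Option available |
| --- | --- | --- |
| 0 | 1 | none |
| 1–19 | 19 | under a quarter |
| 20–38 | 19 | up to half |
| 39–57 | 19 | up to three quarters |
| 58–76 | 19 | no option |
| 77 | 1 | whole |

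Of the 78 possible counts (0 to 77), 78 − 19 = 59 have exactly one band and 19 have none. The gap runs from 58/77 = 75.3% to 76/77 = 98.7%. These are shares of possible page counts, not of women.

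**Step 3: read the options literally.** If an "up to" option includes everything below it, 1–19 pages fit three options and 20–38 pages fit two. This overlap disappears on the ascending reading; the gap does not.

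**Step 4: effect on the whole-booklet share.** Let *t* be the true share who read everything, *g* the share in the gap, *m* the share who read more than half and up to three quarters, and *a* the fraction of gap readers who tick the whole booklet.

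- Recorded whole share = *t* + *a·g*, which lies between *t* and *t + g*.
- Recorded three-quarters share = *m* + (1 − *a*)·*g*.
- Sum of the two = *t* + *m* + *g*, whatever *a* is.

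The bias in the whole share is therefore zero at best and *g* at worst. On the ascending reading, the two top bands combined still give the share who read more than half.

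Illustration with assumed values *t* = 30%, *g* = 20% and all 60 controls answering: the recorded whole share lies between 18/60 = 30% (Wilson 95% interval 19.9 to 42.5%) and 30/60 = 50% (37.7 to 62.3%).

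**Step 5: effect on a mean percentage read.** Assume answers of 10/20/20/20/30% across the five options.

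- If every answer is accurate, the lower bound is 0.2×0 + 0.2×25 + 0.2×50 + 0.3×100 = 45.0%, and the upper bound is 0.2×25 + 0.2×50 + 0.2×75 + 0.3×100 = 60.0%.
- If gap readers may sit in either top band, the lower bound is 0.2×0 + 0.2×25 + 0.2×50 + 0.3×75 = 37.5%, and the upper bound is 0.2×25 + 0.2×50 + 0.2×100 + 0.3×100 = 65.0%.

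In this example the range widens from 15.0 to 27.5 percentage points.

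**The case against.** The strongest reply is that this is a descriptive self-report, asked once at Week 32, where page-level precision means little, and that the plan asks for nothing the item cannot give. Neither section defines the percentage read as a mean or an exact value. The share of controls choosing each option, with a confidence interval, can be computed. The proportion reading any of the booklet is clean because the option for none is unambiguous. The share reading everything is not a quantity the plan names. Most of this stands, and it limits the point to the meaning of the two top bands.

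The same reply disposes of some stronger readings:

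- A reader might infer that the percentage read cannot be obtained at all. It can, in bands.
- A reader might infer that the nested wording spoils the lower bands. With one choice on an ascending scale, most women will read them in order; missing lower limits are a wording weakness only.
- A reader might infer that this item alone describes what controls received, or decides whether the booklet is a credible comparator. Appendix 10 also asks about prior familiarity, helpfulness, reasons for not reading and other support sought, and the protocol attaches no threshold to this figure.

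What the reply does not answer is the gap itself. Reporting the distribution over the printed options does not tell the reader where the near-complete readers went.

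**Conclusion.** The point holds as a modest measurement defect. The item has no option for 58 to 76 of 77 pages, and it is the only quantitative source shown for a named control-arm measure. The percentage read will be available only as ranges, and the two highest bands cannot be interpreted separately.

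The share recorded as reading the whole booklet may be overstated by anything from nothing to the full share of women in the gap. It is tempting to call that share distorted or to put a number of women on it. The documents support neither: they do not say how many women will nearly finish the booklet or which box those women will choose. If all of them tick the lower option, the whole share is right and the three-quarters band is inflated instead. The percentages in steps 4 and 5 illustrate the mechanism under assumed values and are not estimates.

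**What to change.** In Appendix 10, replace the options with exclusive and exhaustive bands: none; less than a quarter; a quarter to less than half; half to less than three quarters; three quarters or more but not all; the whole booklet. All 78 page counts then fall in exactly one band. A banded item still gives a range, so if a numeric percentage is wanted, ask for a figure from 0 to 100% instead.

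In sections 5.6.1.1 and 7.1.1.1, state that the distribution over these bands (or the mean, if the 0 to 100% entry is used) will be reported for the control arm with confidence intervals.

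The cost is one questionnaire item and a line in each of two sections, through whichever amendment route applies; Appendix 30 shows that the follow-up questionnaires were already amended once, in version 3. The downside is that any Week 32 answers already collected on the old scale must be reported separately, or with the top two bands combined as a range. That splits a control arm of 60 across two scales. If most Week 32 forms are already in, the corrected item is mainly of use to the definitive trial.

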**12.15 Appendix 15: Interview Schedule: Control Participants Finished Study**

For participants who were randomised to the control group and completed the whole study (i.e., completed the last questionnaire).

- First of all, how have you found taking part in this study?
- Did you feel that the information provided about the study was clear?
  - Were you able to understand what taking part would involve?
- How did you find the contact and communication from the research team throughout the study?
  - Was each stage of the research (e.g., each questionnaire) clear?
  - Did you feel comfortable corresponding with them?
- How did you feel about the 50% chance that you would be able to attend the body image programme (i.e., being randomised)?
  - How did you feel when you were told that you would not be attending the body image programme?
  - What made you decide to continue with the study, despite not being allocated to the body image programme?
- What did you think of the Macmillan booklet that you were given?
  - Were you aware of this booklet?
  - Did you read the whole Macmillan booklet?
  - Did you find it helpful/unhelpful? Why?
- Did you access any other form of support in relation to your body image?
  - What was this?
  - Was it helpful/unhelpful? Why?
- How did you find completing the questionnaires throughout the study? *(share the questionnaire to remind them of the questions)*
  - What did you think of the format by which you completed these (either paper or online). How could this be improved?
  - How did you find the time it took to complete each questionnaire?
  - How did you find the instructions for completing the different questions in the questionnaire?
  - Did you feel that the questions that you were asked were relevant?
  - Were there other impacts of your body image concerns that were not explored or asked about in the questionnaires?
- What else could we do to help encourage women to take part in a future study and to stay until the end?
- Do you have anything else to add, or any questions?

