- Yes, always
- Yes, sometimes
- No, never

Did you receive chemotherapy?

- Yes
- No

Did you receive radiotherapy?

- Yes
- No

What type of hormonal therapy did you receive?

- Tamoxifen
- Aromatase Inhibitor (e.g. Anastrozole, Exemestane, Letrozole)
- Other (please specify) ____________________
- Not sure
- None

Have you received any other form of treatment that has not already been stated?

- Yes (please state)
- No

Have you received, or are receiving, any form of support (e.g. therapy) to address your body image concerns?

- Yes
- No

If YES, please specify what kind of support you have received or are receiving.

If YES, how helpful was that support?

|  | Not at all helpful  1 | 2 | 3 | 4 | Very helpful  5 |
| --- | --- | --- | --- | --- | --- |
| Please select one option: |  |  |  |  |  |

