**12.24 Appendix 24: Modified version of the Adult Service Use Schedule: T3**

**Accepting your Body after Cancer (ABC)**

**USE OF HEALTH AND SOCIAL CARE SERVICES**

**INSTRUCTIONS**

It would be helpful for us to know what types of health and social care services you have used since you entered the ABC study approximately 5 months ago. These can be services that you received in a hospital or in the community (for example, in a GP surgery, a community health centre or in your home).

If you are in the ABC therapy group, please **EXCLUDE YOUR USE OF THE ABC THERAPY**, as it is important that ABC research staff are unaware of who is receiving the ABC therapy.

Some of the services listed in this questionnaire may not be relevant to you, but it would still be helpful for us to know this, so **please select ‘No’ if you have not used any of the services listed**.

We understand that you may not remember the exact number of appointments you have had for the services you have used, but **please give us your best guess**.

1. **HOSPITAL SERVICES INVOLVING AN OVERNIGHT STAY**

We would like to know if you have stayed overnight in hospital since you entered the ABC study approximately 5 months ago.

For each reason listed, please tell us if you have stayed overnight in hospital for this reason by selecting ‘Yes’ or ‘No’.

If the answer is ‘Yes’, please tell us how many nights in total you stayed overnight in hospital for this reason since you entered the ABC study approximately 5 months ago.

If you had overnight stays in a hospital on more than one occasion for the same reason, please report the total number of nights for all occasions.

| **Reason** | **Yes** | **No** | **If yes, please enter the total number of nights you stayed in hospital for this reason since you entered the ABC study approximately 5 months ago** |
| --- | --- | --- | --- |
| **Overnight stay in hospital for reasons related to cancer** |  |  |  |
| **Overnight stay in hospital for reasons related to your mental health** |  |  |  |
| **Overnight stay in hospital for any other reason** |  |  |  |

1. **HOSPITAL SERVICES THAT DID NOT INVOLVE AN OVERNIGHT STAY**

We would like to know if you have had any appointments in hospital since you entered the ABC study approximately 5 months ago. These are hospital appointments where you DID NOT stay in hospital overnight and are commonly called outpatient or day-patient appointments.

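### Appendix 10's question on other body-image support does not exclude ABC, so the two arms' answers may not be comparable

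*Protocol*

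**What the plan says.** Appendix 10 (Research Process Feedback) is "to be completed by all participants in the six-month post-intervention assessment i.e., Week 32" (Protocol, section 5.6.1.2). After some general items it asks four questions about the Macmillan booklet, ending with "If you did not read any of the booklet, could you please tell us why". The Yes/No item "Did you seek any other support for your body image during the study" comes next. Two follow-ups are attached: an open question, "If you did seek other support, could you please tell us what this was", and a 1 to 5 rating, "How helpful did you find this support". ABC is first named in the item after these, on allocation to the other condition.

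Section 6.1 says that the ABC arm is also sent the booklet. The service-use forms at T3 and T4 (Appendices 24 and 25) tell women in the ABC group to leave ABC out of their answers; the reason given is "as it is important that ABC research staff are unaware of who is receiving the ABC therapy". The interview schedules for completers (Appendices 15 and 16) ask "Did you access any other form of support in relation to your body image". In the ABC-arm schedule that question comes after the questions on both ABC and the booklet.

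Section 7.1.1.2 plans descriptive summaries (means, standard deviations, percentages) of the rating scales on the research process.

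**The concern.** The word *other* needs a reference point, and the form supplies only the booklet. For a control, the item then covers anything beyond the booklet. For a woman in the ABC arm, read in sequence, it covers anything beyond the booklet including ABC itself, which was body-image support given during the study. One question can thus carry two meanings, and the meaning depends on allocation.

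This is the only closed question put to both arms after randomisation about support specifically for body image. The service-use forms count contacts by type of service, not by body-image purpose. Section 6.3 justifies the booklet control partly on the ground that no usual care exists for this problem, and section 2 lists women's experience of being in each arm among the uncertainties to resolve. Whether booklet-only women look elsewhere more often than ABC women is therefore useful for choosing the control in the definitive trial. Extra Yes answers in the ABC arm could mask such an excess. A helpfulness score given to ABC would also be tabulated as a score for outside support.

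**Working it through.** The plan states no figure for this item, so there is none to reproduce. The check is on wording, followed by an illustration.

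**Instruments side by side**

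| Instrument | Who answers | Is ABC excluded? |
|---|---|---|
| Appendix 10 item (T4) | Both arms | No; only the booklet has been named |
| Service-use forms (T3, T4) | Both arms | Yes, by explicit instruction |
| Completer interview, ABC arm (Appendix 16) | Interviewed subset | By position, after the ABC and booklet questions |

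Appendix 10 has neither safeguard.

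**Illustration of size**

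Let *p* be the true proportion using other support, the same in both arms. Let *m* be the share of the remaining ABC-arm women who count ABC. Both are assumptions; the documents give neither. The arm size of 60 is from section 3, with every woman assumed to respond at Week 32.

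Observed ABC-arm rate = *p* + (1 − *p*)*m*. Gap against control = (1 − *p*)*m*.

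With *p* = 20%:

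| *m* | ABC-arm rate | Gap (points) | Extra Yes of 60 |
|---|---|---|---|
| 0% | 20% | 0 | 0 |
| 5% | 24% | 4 | 2.4 |
| 10% | 28% | 8 | 4.8 |
| 25% | 40% | 20 | 12 |
| 50% | 60% | 40 | 24 |

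For *p* from 10% to 30% and *m* from 5% to 50%, the gap runs from 0.70 × 0.05 = 3.5 points to 0.90 × 0.50 = 45 points.

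For scale, the 95% half-width of the difference at 28% against 20% is 1.96 × √[(0.28 × 0.72 + 0.20 × 0.80)/60] = 15.2 points. An 8-point gap lies well inside it.

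**Effect of the free text**

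Let *u* be the share of misclassified Yes answers whose free text is blank or too vague to recode. The gap left is (1 − *p*)*m* × *u*. It is zero if every such answer names ABC, and equals the table's figure only if none does. With *p* = 20% and *m* = 25%, it is 20 × *u* points.

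**The verb**

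If a share *f* of seekers obtain support, the reported rate is the received rate divided by *f*. With 20% receiving, *f* = 75% gives 26.7% and *f* = 50% gives 40%. With equal *f* this happens in both arms alike, so it creates no gap between them.

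**The case against.** The strongest objection is that women may not read the item this way. ABC was allocated, not looked for, and the natural sense of seeking is support a woman found for herself. The same T4 assessment asks ABC women separately about the programme (Appendix 31) and gives them the service-use form with its ABC exclusion. The order of the forms is not stated, but these may cue the intended reading. This stands, and it is why the share counting ABC is unknown and may be zero.

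The next line of the form also asks what the support was. That stands too: the gaps in the table are before recoding. What remains is the blank or vague answers, and answers that mix ABC with something else, where the Yes is sound but the helpfulness score is not.

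The service-use exclusion is there to keep staff unaware of allocation, not to classify outside support. So Appendix 10 does not contradict those forms; they show only that an explicit exclusion is practicable. They also count talking therapy, cancer support specialists and charity support in both arms, so knowledge of outside support does not rest on this item alone.

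Three stronger readings are tempting and not supported:
- **That the ABC-arm rate is inflated.** Nothing in the documents shows that any woman would count ABC.
- **That asking what was sought separates the arms.** The verb is the same for both, and the drop-out schedules (Appendices 13 and 14) use it as well.
- **That change from baseline is distorted.** No such comparison is planned. The baseline item (Appendix 17), "Have you received, or are receiving, any form of support (e.g. therapy) to address your body image concerns", has no recall window, so matching the verbs would not make the two comparable.

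**Conclusion.** The fault holds as a minor one. The item can mean different things in the two arms because it follows only booklet questions and does not exclude ABC. The Yes percentage and its helpfulness rating may therefore not be comparable between arms. No size can be given: the range runs from zero upwards, the gaps shown rest entirely on assumed values of *p* and *m*, and recoding would remove most of any error where the free text is completed. The protocol defines no rate of outside support and no between-arm test from this item. What is affected is the reading of a descriptive result that bears on the choice of control, not a feasibility outcome or the analysis of the validated measures.

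**What to change.** In Appendix 10, open the item with *Apart from the Macmillan booklet and, if you were in that group, the ABC programme*, and widen the verb to *seek or receive*. The exclusion makes the arms comparable. The wider verb only lets in support offered unasked, and it applies equally to both arms. Put the same exclusion on the helpfulness rating.

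For forms already returned, recode from the free text, set aside helpfulness scores that refer to ABC, and report by arm how many Yes answers name ABC and how many have blank text.

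The cost is a small amendment to one form and its online version. If some T4 forms are already in, there will be two versions of the item, and the report should say which women answered which. If the sponsor prefers not to change the form during the study, recoding can be done alone and the wording corrected before the form is reused in the definitive trial.
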